### 2.3. Sample Size Calculation

Sample size was calculated using G*Power software 3.1.9.7© (Germany) [30]. In order to detect differences in quality of life in favor of the EG, a large effect size of d = 0.80, an error α = 0.05, and a power of 90% were assumed. Considering a possible loss to follow-up of 10%, the sample size results in 62 participants.

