### 2.9. Statistical Analysis

The Statistical Package for the Social Science software (SPSS^®^ v25) for Mac will be used. An intention-to-treat analysis will be performed. Tests will be carried out with a 95% confidence interval and a statistical significance level of *p* < 0.05. First, descriptive analysis will be performed using means and standard deviations or medians and interquartile ranges otherwise. Normality will be studied through Kolmogorov–Smirnov’s test. For nominal qualitative variables, absolute and relative frequencies will be used. The homogeneity of descriptive and baseline data will be analyzed through Student’s *t*-test for independent samples, Welch’s *t*-test, or the Mann–Whitney U-test. In the case of qualitative variables, Pearson’s χ2 or Fisher’s exact test will be used. Baseline differences will be adjusted through covariate adjustment in regression models. ANCOVA might also be performed to control for baseline differences while comparing the means of the outcome between groups.

To analyze within-group differences between baseline, 6-week, and 6-month assessments, repeated-measures ANOVA or Friedman’s ANOVA will be carried out. To estimate the effect size, partial eta squared will be used. On the other hand, to study the differences between groups, Student’s *t*-test for independent samples, Welch’s *t*-test, or the Mann–Whitney U-test will be carried out. The effect size will be estimated using Cohen’s d or following Grissom’s criteria [47,48,49] in the case of the Mann–Whitney U-test.

Finally, the possible effect of the interaction between descriptive data and independent variables (EG and CG) on the dependent variables will be analyzed through ANCOVA, estimating the effect size using partial eta squared.

Intention-to-treat analysis will be performed in order to reduce, among others, the attrition bias and selection bias that could distort the results. Sensitivity analysis will also be performed in order to address the impact of missing data and ensure the results are as reliable and unbiased as possible.

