The hypothesis of this study posits that the PT intervention designed and proposed for the EG will be more successful for recovery outcomes, particularly in terms of functionality, quality of life, and participation. To validate this hypothesis, specific outcome variables will be meticulously measured using tailored assessment tools designed for Stroke survivors. This approach ensures that the data collected are both relevant and sensitive to the unique challenges faced by this population [54].

This study will include a significant sample size of 62 individuals aged 50 or older. This demographic is particularly relevant as the incidence of Stroke significantly increases within this age range [4]. Additionally, the study participants will have a post-Stroke evolution time of at least six months. This duration is considered sufficient for individuals to have a clearer understanding and awareness of the changes in their functional abilities, social engagement, and overall quality of life.

The number of sessions, their frequency, and their duration in this study are determined based on established guidelines from the literature and experts’ recommendations [7,55,56,57]. These parameters are carefully chosen to align with best practices in Stroke rehabilitation, ensuring that the intervention is both evidence-based and practical for implementation.

As a novel aspect, the achievement of functional goals is included as an outcome variable. This decision is informed by recommendations from existing research, which underscores the importance of goal attainment in the rehabilitation process [52]. While the measurement of functional goal achievement is recognized as a valuable indicator of rehabilitation success, it has seldom been evaluated prospectively in previous studies. This study aims to fill that gap by rigorously tracking and assessing the extent to which participants meet their individualized functional goals over the course of the intervention and follow-up period. The assessment of functional goals will also contribute valuable data to the field of Stroke rehabilitation, potentially highlighting the importance of goal-oriented approaches in enhancing patient outcomes [20].

This study may face some limitations such as the lack of adherence for the duration of this study and further complications because of the age of the participants.

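### The main tests named use only observed or complete outcomes by default, so they do not themselves give the protection against attrition bias claimed for intention-to-treat

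*Protocol article*

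**What the plan says.** Section 2.9 of the protocol article commits to intention-to-treat twice, the second time with its purpose: "Intention-to-treat analysis will be performed in order to reduce, among others, the attrition bias and selection bias that could distort the results". The next sentence adds: "Sensitivity analysis will also be performed in order to address the impact of missing data". No method is named for that sensitivity analysis.

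The same section assigns tests to tasks:
- Change within each group over the three assessments: repeated-measures ANOVA or Friedman's test.
- Differences between groups: Student's t, Welch's t or Mann–Whitney.
- Adjustment for baseline imbalance: regression with covariates, and possibly ANCOVA.
- Interaction of descriptive variables with arm: ANCOVA.

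Section 2.3 plans for attrition: "Considering a possible loss to follow-up of 10%, the sample size results in 62 participants". Outcomes are measured at baseline (A0), at the end of the 10-week programme (A1) and six months after baseline (A2), according to section 2.7.

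**The concern.** Intention-to-treat says which arm a participant is analysed in. It does not say what happens when the outcome is missing. Protection against attrition bias has to come from the method of analysis, and by default none of the named methods takes in a participant whose outcome was not observed. Missing data are mentioned only under the sensitivity analysis, which comments on the main result but does not alter it.

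Two things follow if the tests are run as named. If those lost differ from those who stay, and do so differently in the two arms, the arm difference is biased. Also, a between-group test at A2 makes no use of the A1 score of someone lost between the two visits, although that score carries information about the missing value. The programme has three sessions a week for 10 weeks and a further assessment at six months, so loss related to how a participant is doing is plausible.

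**Working it through.** **1. The plan's own sample size.** Section 2.3 gives "a large effect size of d = 0.80, an error α = 0.05, and a power of 90% were assumed"; section 2.5 gives 1:1 allocation; the loss allowance is 10%. Sidedness is not stated, though the aim is worded directionally: "In order to detect differences in quality of life in favor of the EG". Two-sample t-test, noncentral t:
- One-sided: 28 per arm, 56 in total; 56 × 1.10 = 61.6, rounded up to 62. This matches the plan. Dividing instead gives 56 / 0.90 = 62.2, rounded up to 63.
- Two-sided: 34 per arm, 68 in total; 68 × 1.10 = 74.8, or 75; 68 / 0.90 = 75.6, or 76. Neither gives 62.

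So 62 is 56 evaluable participants plus the allowance, on a one-sided reading.

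**2. Is power lost?** With 10% lost and nothing imputed, 62 × 0.90 = 55.8, about 56, which is the number the calculation was built on. Power at d = 0.80:

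| Observed per arm | One-sided | Two-sided |
|---|---|---|
| 28 | 90.5% | 83.6% |
| 31 | 92.9% | 87.3% |

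The one-sided power at 28 per arm meets the planned 90%. The row for 31 is an upper bound on what a better method could recover, since no model or imputation restores all lost information. Loss at the planned rate does not undercut the plan's own power.

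**3. What each named test uses by default.**

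| Test (section 2.9) | Task | Data used by default |
|---|---|---|
| Repeated-measures ANOVA, Friedman | within-group change | participants with all three assessments |
| Student's t, Welch, Mann–Whitney | between groups | participants observed at that visit |
| Regression, ANCOVA | adjustment, interaction | participants with outcome and covariates observed |

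Deleting anyone with a missed visit therefore affects the within-group results. A participant seen at A1 and lost by A2 still counts in the arm comparison at A1 and is absent only from the one at A2.

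**4. Possible size of the bias.** The documents give no outcome data for those lost, so this step rests on assumptions. Let p be the fraction of an arm that is lost and δ the amount, in SD, by which those lost are worse than that arm's completers. The full-arm mean is (1 − p) × completer mean + p × (completer mean − δ) = completer mean − pδ, with scores oriented so that higher is better. The observed mean is too good by pδ, and the arm difference shifts by the experimental-arm pδ minus the control-arm pδ.
- p = 0.10 in one arm only, δ = 0.5: 0.10 × 0.5 = 0.05 SD; 0.05 / 0.80 = 6.25% of the planned effect.
- p = 0.10 in one arm only, δ = 1: 0.10 × 1 = 0.10 SD; 0.10 / 0.80 = 12.5%.
- The same p and δ in both arms: net shift zero.

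Loss in the experimental arm would flatter the intervention; loss in the control arm would work against it.

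**The case against.** The strongest reply is that a journal article condenses the plan. The rule for missing outcomes is commonly left to the statistical analysis plan, which is not shown, and imputing first and then running the named tests is compatible with the text. That stands: the lack of a named imputation method is no finding. It does not dispose of the point, because the article itself chose the main tests and claimed for the analysis a property that those tests lack by default. A later document would have to supplement or replace them to make the claim true.

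A reader might infer more than the documents support:
- *That the lost participants are dropped, so the main analysis is a completers analysis.* No section says so. The between-group tests keep everyone observed at the visit, and the methods that need all three visits are assigned to within-group change, which does not estimate the arm difference.
- *That the sample size excludes the 10%.* Raising N for possible loss protects power and defines no analysis set.
- *That the article predicts the loss.* The Discussion says "This study may face some limitations such as the lack of adherence for the duration of this study". Adherence is not attrition: a participant who misses sessions can still be assessed and analysed in the assigned arm.
- *That the effect would be 12.5% too favourable.* That is the top of an assumed range, with loss in one arm only.

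It can also be said that a mixed model is no cure. It assumes data missing at random, it learns nothing about the effect from someone missing both A1 and A2, and a linear model does not suit FAC (levels 0 to 5) or GAS (described as a 6-point scale). All of this stands and limits the fix.

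**Conclusion.** The point holds in a limited form. The stated purpose of reducing attrition bias is not tied to any procedure in the main analysis, since the named tests by default use complete or observed outcomes and the sensitivity analysis does not change the main result. The issue is possible bias and inefficient use of the data, not power: about 56 observed participants still give 90.5% one-sided power, the reading on which 62 is reproduced. The possible shift is 0.05 to 0.10 SD, or about 6% to 12.5% of d = 0.80. It assumes 10% loss in one arm with those lost 0.5 to 1 SD worse, and is about zero if loss is similar in both arms. This is an inexpensive improvement worth making before analysis, not a fault that invalidates the trial.

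**What to change.** **Main between-group analysis.** For NewsQoL, Ox-PAQ, Barthel, PASS and TIS, use a likelihood-based linear mixed model (MIXED in the SPSS already named). Analyse participants in their assigned arm, with baseline score, arm, visit and arm × visit, and every available A1 and A2 value. Report the arm difference at each visit from this model. It tests arm by visit directly and lets the A1 score of someone lost before A2 contribute.

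**FAC and GAS.** Use an ordinal counterpart, or keep the rank-based test and say that it covers only those observed.

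**Sensitivity analysis.** Because the model assumes missing at random and gains nothing from people missing both A1 and A2, specify the promised analysis as multiple imputation with a worse-outcome shift for those lost. A shift range of 0.5 to 1 SD would match the illustration above. State in one sentence how participants without any outcome after baseline are handled.

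**Cost.** Slightly more analysis work and an explicit missing-at-random assumption in the main model. No new data, no change in N and no new software.

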## 3. Discussion

The aim of this study is to evaluate the effectiveness of a PT intervention that emphasizes functional goal-directed and task-specific training. The primary focus is to assess improvements in functionality, participation, and quality of life for individuals who have had a Stroke. According to the authors’ knowledge, this is the first study to implement a person-centered intervention that integrates goal-directed and task-specific approaches in order to measure the impact on participation and quality of life for Stroke survivors. Therefore, this study intends to bridge the gap in current research by not only assessing traditional functional outcomes, but also focusing on the broader aspects of participation and quality of life. The intervention is designed to be tailored to the individual needs and goals of each participant, reflecting a holistic approach to rehabilitation that goes beyond conventional PT practices. By measuring outcomes related to participation, this study seeks to provide a comprehensive understanding of how these specialized interventions can facilitate reintegration into daily and social activities and enhance overall well-being. The findings of this study could have significant implications for the development of more effective, personalized intervention protocols for Stroke survivors.

Participation and quality of life perception are closely related aspects that are fundamental to a person’s recovery after having a Stroke. Evidence suggests that, within the first three months post Stroke, individuals often express dissatisfaction with their ability to participate in social and daily activities [9]. This dissatisfaction frequently persists over the long term, emphasizing the need for intervention in this area. Despite this, contemporary models of PT interventions usually tend to concentrate primarily on body structure and function impairments and improving gait mobility, motor control, and balance [7,21,24]. Most of these interventions operate under the assumption that enhancements in these areas will naturally lead to a restoration of functionality and the impact on other areas. There is growing recognition that interventions should not be limited to addressing impairments in body structure and function. Instead, they should also emphasize enhancing participation and quality of life [17,18,19]. This holistic approach acknowledges that true recovery encompasses more than just physical rehabilitation; it involves enabling individuals to engage fully in their desired activities and social roles [50]. Therefore, PT interventions should be designed to support not only the physical rehabilitation of Stroke survivors but also their reintegration into the community and social life [51]. By prioritizing participation and quality of life, these interventions can more effectively address the comprehensive needs of Stroke survivors, helping them to regain a sense of autonomy and fulfillment in their everyday lives. This shift in focus is essential for developing a more inclusive and person-centered approach to Stroke rehabilitation [17,18,19].

In contemporary rehabilitation practice, there is a growing trend towards PT interventions that are based on person/family-centered approaches. These approaches emphasize functional goal-oriented and task-specific training, aiming to empower patients and actively involve them in their recovery. Such methodologies not only encourage patients to take an active role in their therapeutic process but also stimulate their motivation, which is crucial for sustained engagement and progress during recovery [15,22,23,24,25]. The literature supports the effectiveness of person-centered goal setting within Stroke interventions, considering that it is feasible and beneficial. These approaches allow the customization of the treatment program to be aligned with the individual needs, preferences, and goals of each person, thus enhancing the relevance and impact of the interventions. Despite the recognized advantages, this practice is not yet widely implemented in clinical settings. The underutilization of person-centered goal setting may be attributed to a variety of factors, including traditional training models, time constraints, and a lack of resources or awareness among healthcare providers [52]. To optimize Stroke intervention outcomes, it would be advisable that more PT practitioners adopt and integrate person-centered strategies. This shift could lead to more tailored and effective interventions that address physical impairments and support patients’ psychological and emotional well-being. By creating a more collaborative therapeutic environment, these approaches can help patients achieve meaningful recovery goals, thereby improving their overall quality of life and satisfaction with the recovery process.

Some PT interventions focus specifically on primary impairments of Stroke, such as spasticity and/or muscle weakness, and it seems that there is not enough evidence on functionality improvement [53]. Therefore, interventions that prioritize the use of active strategies that combine the analysis of movement patterns with training of functional tasks show improvements not only in functionality, but also in muscle strength and/or spasticity [7,21,22,23,24]. The aim of this study, based on the ICF [12,13,14], is addressing secondary impairments that are significant to Stroke survivors, rather than addressing only primary impairments such as spasticity and muscle weakness, although this does not mean that they are not addressed indirectly.

The hypothesis of this study posits that the PT intervention designed and proposed for the EG will be more successful for recovery outcomes, particularly in terms of functionality, quality of life, and participation. To validate this hypothesis, specific outcome variables will be meticulously measured using tailored assessment tools designed for Stroke survivors. This approach ensures that the data collected are both relevant and sensitive to the unique challenges faced by this population [54].

This study will include a significant sample size of 62 individuals aged 50 or older. This demographic is particularly relevant as the incidence of Stroke significantly increases within this age range [4]. Additionally, the study participants will have a post-Stroke evolution time of at least six months. This duration is considered sufficient for individuals to have a clearer understanding and awareness of the changes in their functional abilities, social engagement, and overall quality of life.

The number of sessions, their frequency, and their duration in this study are determined based on established guidelines from the literature and experts’ recommendations [7,55,56,57]. These parameters are carefully chosen to align with best practices in Stroke rehabilitation, ensuring that the intervention is both evidence-based and practical for implementation.

As a novel aspect, the achievement of functional goals is included as an outcome variable. This decision is informed by recommendations from existing research, which underscores the importance of goal attainment in the rehabilitation process [52]. While the measurement of functional goal achievement is recognized as a valuable indicator of rehabilitation success, it has seldom been evaluated prospectively in previous studies. This study aims to fill that gap by rigorously tracking and assessing the extent to which participants meet their individualized functional goals over the course of the intervention and follow-up period. The assessment of functional goals will also contribute valuable data to the field of Stroke rehabilitation, potentially highlighting the importance of goal-oriented approaches in enhancing patient outcomes [20].

This study may face some limitations such as the lack of adherence for the duration of this study and further complications because of the age of the participants.

## 4. Conclusions

This study could provide valuable insights into the effectiveness of person-centered, goal-directed, and task-specific interventions, offering further understanding of how these approaches can be optimized to support Stroke survivors in achieving meaningful recovery.

## Figures and Tables

**Figure 1 jpm-14-00891-f001:**
[figure not shown]
Consort diagram: flow of participants throughout this study.

**Table 1 jpm-14-00891-t001:** Sociodemographic variables.

Variable	Values
Age	Years
Sex	Man/Woman
Stroke evolution time	Months
Work status prior to the Stroke	Employed/Unemployed
Actual work status	Employed/Unemployed
Type of Stroke suffered	Ischemic/Hemorrhagic
Most affected hemibody	Right/Left
Other comorbidities	Yes/No

## Data Availability

The data generated in this study will be included in the results of the published article.
